# Memantine and graded motor imagery for complex regional pain syndrome (MEMOIR): study protocol and statistical analysis plan for a decentralised, 2 × 2 factorial randomised trial

**DOI:** 10.1186/s13063-025-09383-8

**Published:** 2025-12-29

**Keywords:** Complex regional pain syndrome, Memantine, Graded motor imagery, Factorial, Chronic pain

## Abstract

**Background:**

Complex regional pain syndrome (CRPS) is a rare chronic pain condition characterised by severe pain, sensory, motor, autonomic, and trophic abnormalities. Effective treatment options are limited, and international guidelines rely on low-quality evidence and consensus. Two interventions—memantine, an N-methyl-D-aspartate receptor antagonist, and graded motor imagery, a rehabilitation approach targeting sensorimotor processing—have shown promise in pilot studies but lack definitive evaluation in large-scale trials. MEMOIR aims to evaluate the benefits and harms of memantine and graded motor imagery for CRPS.

**Methods:**

MEMOIR is a fully decentralised, 2 × 2 factorial, randomised trial comparing memantine with placebo and graded motor imagery with no graded motor imagery in adults with CRPS. A total of 204 participants with CRPS of 6 months to 5 years duration will be randomised to one of four groups: (i) memantine and graded motor imagery, (ii) memantine only, (iii) placebo and graded motor imagery, or (iv) placebo only. Memantine will be administered at 40 mg/day (or maximum tolerated dose); graded motor imagery will comprise seven 1-h sessions delivered via telehealth. The treatment period is 16 weeks. The dual primary outcomes are pain intensity (11-point numeric rating scale) and PROMIS pain interference assessed at 16 weeks. Secondary outcomes include physical function, fatigue, cognitive function, depressive symptoms, self-efficacy, health-related quality of life, CRPS severity, healthcare use, and adverse events. The follow-up period is 52 weeks. The estimands of interest are the mean effect of memantine compared to placebo and the mean effect of graded motor imagery compared to no graded motor imagery on all outcomes. All analyses will follow the intention-to-treat principle.

**Discussion:**

MEMOIR will be the largest investigator-initiated CRPS trial to date. The 2 × 2 factorial design and decentralised delivery aim to maximise efficiency, accessibility, and equity. If effective, memantine and graded motor imagery represent scalable, low-cost treatments that can be given in clinics or at home, with the potential to transform CRPS management.

**Trial registration:**

Australian New Zealand Clinical Trials Registry (ACTRN12621000175875). Registered on 12 February 2021.

**Supplementary Information:**

The online version contains supplementary material available at 10.1186/s13063-025-09383-8.

## Introduction

### Background and rationale {6a}

Complex regional pain syndrome (CRPS) is a rare pain disorder that usually occurs in a single limb following trauma, such as fracture or surgery [1]. CRPS is characterised by severe pain and sensory, vasomotor, sudomotor, motor and trophic signs and symptoms [1, 2]. The pathophysiological mechanisms of CRPS are incompletely understood, but likely involve aberrant inflammatory and immune responses, vasomotor dysfunction, nervous system changes, genetic variations, and psychological processes [3]. CRPS is classified as a chronic primary pain disorder in the International Classification of Diseases Volume 11 (ICD-11) [2, 4].

CRPS incidence is estimated at between 6 and 26 per 100,000 person-years, meeting US Food and Drug Administration and European Medicines Agency rare disease definitions [5–8]. The disorder is most common in people aged between 50 and 80 years, and affects four females for every male [3]. Data from prospective studies are limited but suggest that while CRPS typically improves rapidly in the first 6 months following symptom onset [9, 10], ongoing pain and motor dysfunction at 12 months and beyond are common [11]. People with persistent CRPS report poor quality of life [12], increased depressive symptoms [13], and reduced work status [11].

Effective treatment options for CRPS are limited. International clinical guidelines recommend multidisciplinary care that includes pharmacological, interventional, psychological, and rehabilitation therapies [14]. However, recommendations are informed by low-quality evidence and consensus. A 2023 Cochrane overview of systematic reviews identified no interventions for CRPS whose efficacy or effectiveness are supported by high- or moderate-certainty evidence [15]. This overview highlighted a critical need for adequately powered, high-quality randomised controlled trials of pharmacological and non-pharmacological interventions, selected based on rigorous pilot research or major clinical uncertainty [15]. It also identified preliminary evidence of effectiveness for two interventions: memantine and graded motor imagery [16–18].

Memantine is a non-competitive N-methyl D-aspartate receptor antagonist (NMDA) approved for treatment of moderate-to-severe Alzheimer’s disease. It is proposed to reduce pain intensity by blocking sustained glutamatergic NMDA receptor activity in central nervous system nociceptive pathways [19–21]. A pilot trial of 20 patients with CRPS showed that, compared with placebo, a 7-week course of 40 mg/day of oral memantine provided clinically important reductions in pain intensity with no between-group differences in adverse events [16]. However, that study was not powered to robustly evaluate efficacy and safety.

Graded motor imagery is an established rehabilitation intervention for CRPS. It aims to reduce pain and improve function through a graded progression of movement imagery, mirror therapy, and functional tasks that target cortical processing of the affected limb [22]. A 2022 Cochrane review found that, compared with treatment as usual, a 6-week graded motor imagery program provided clinically important reductions in pain intensity (mean difference [on a 0–100 scale] −21.0 [95% confidence interval −31.2 to −10.9], 2 studies; 49 participants) [23]. However, previous studies were small, at high risk of bias, and did not assess long-term effects. Despite endorsement in international clinical guidelines [24–27] and widespread use, uncertainty regarding the effectiveness of graded motor imagery remains.

MEMOIR (MEmantine and graded MOtor Imagery for complex Regional pain syndrome) aims to evaluate the benefits and harms of memantine and graded motor imagery for CRPS.

### Objectives {7}

The primary objectives of the MEMOIR trial are to estimate the effects of (i) memantine compared to placebo and (ii) graded motor imagery compared to no graded motor imagery, on pain intensity and pain interference at 16 weeks. Secondary objectives are to estimate the sustained effects of memantine and graded motor imagery on pain intensity and pain interference at 26 and 52 weeks, and immediate and sustained effects of the following outcomes at 16, 26, and 52 weeks: physical function, fatigue, self-efficacy to manage symptoms, cognitive function, depressive symptoms, health-related quality of life, pain self-efficacy, patient global impression of change, CRPS severity score, healthcare use, and adverse events.

### Trial design {8}

MEMOIR is a fully decentralized, 2 × 2 full-factorial, randomized trial with four parallel groups allocated at a 1:1:1:1 ratio to (i) memantine and graded motor imagery; (ii) memantine only; (iii) placebo and graded motor imagery; and (iv) placebo only. All outcomes for each main comparison (memantine versus placebo; graded motor imagery versus no graded motor imagery) are tested for superiority. A 2 × 2 factorial design was chosen because there is little reason to expect an interaction between interventions (that is, there is little reason to expect the effects of either intervention, expressed as an absolute difference, depend on the presence or absence of the other intervention). In the absence of an interaction between interventions, a factorial design provides an efficient way to evaluate the effects of two interventions. This protocol and statistical analysis plan is reported in accordance with the Standard Protocol Items: Recommendations for Interventional Trials (SPIRIT) statement and the extension for factorial randomized trials [28–30].

## Methods: participants, interventions, and outcomes

### Study setting {9}

MEMOIR is a decentralised trial (i.e. a trial that uses procedures conducted outside the traditional clinical trial site) [31, 32], conducted in the community, Australia-wide. Participants will undergo all recruitment, screening, and treatment activities at their home setting.

### Eligibility criteria {10}

#### Inclusion criteria

Diagnosis of unilateral CRPS according to the Budapest research criteria, of 6 months to 5 years durationAt least moderate pain and disability as measured using the Short Form Health Survey [33] items 7 and 8Aged 18 years and olderEnglish language proficiencyAccess to internetWillingness to provide informed consent and to comply with the study requirements

#### Exclusion criteria

Women who are pregnant or lactatingParticipants who are female, of child-bearing potential and not using reliable contraceptive method(s)Males and females planning conceptionKnown allergies to NMDA receptor antagonistsUsing >60 mg/day morphine equivalents of opioid analgesicsUsing methadoneUsing >450 mg/day of pregabalin or >1200 mg/day gabapentinUsing monoamine oxidase inhibitorsUsing >50 mg/day of tricyclic antidepressantsUsed ketamine in the preceding 4 weeksReceived lidocaine injections or infusions in the preceding 4 weeksCommenced bisphosphonate treatment in the preceding 4 monthsUsing anti-arrhythmic cardiac medicationsUsing anti-psychotic medicationsUsing cisapride, erythromycin, or quinolonesUsing anti-tuberculous or anti-fungal agentsUsing antiretroviralsModerate to severe renal impairment (defined as estimated glomerular filtration rate below 70 mL/min/1.73 m^2^)Prolonged QTc syndrome, ventricular fibrillation, ventricular tachycardia, heart block, or Torsades de PointesAcute coronary syndrome in the preceding 3 monthsNYHA classes III–IV heart failureUncontrolled hypertensionPacemaker or implantable defibrillatorHistory of neurological conditions (e.g. seizure disorders, Alzheimer’s disease, paralysis, stroke)History of schizophrenia, psychosis, bipolar disorder, or clinically significant delusions, hallucinations, or deliriumSignificant history of illicit substance abuse or drug overuseImplanted spinal cord or nerve stimulatorsOther pain that may interfere with assessment of CRPS and/or use of graded motor imagery, according to the study physicianCurrently using graded motor imageryScheduled for major surgery during the treatment or follow-up period

Participants must meet all inclusion criteria to allow randomisation to all treatment factors. Participant screening is conducted in 3 stages: (i) online using a REDCap screening form [34, 35]; (ii) via telephone with a trained research assistant; and (iii) via telehealth with a specialist pain physician.

### Who will take informed consent? {26a}

Potential participants will receive a written participant information statement that outlines the study objectives, procedures, and potential risks and benefits. They will be instructed to take at least 24 h to read the information statement and discuss their participation in the trial with a relative or a friend. A research assistant trained in ICH Good Clinical Practice [36] and the consent procedures will discuss the trial in light of the information provided in the statement and answer any questions about the trial the potential participant might have. Participants willing to consent will be provided with a REDCap eConsent form. Upon completion of the REDCap eConsent form, a static PDF copy of participant consent responses will be stored in the REDCap project’s file repository and emailed to the participant. The consent-specific PDF will have the values of the eConsent framework options inserted in each page of the PDF. These values (i.e. name, date of birth) are added to the PDF as documentation of the identity of the person who is consenting. Participants enrolled in the study will also have the opportunity to provide consent to Services Australia for the release of Medicare Benefits Schedule (MBS) and/or Pharmaceutical Benefits Scheme (PBS) data to allow for healthcare use and cost-effectiveness evaluations.

### Additional consent provisions for collection and use of participant data and biological specimens {26b}

Participants may be invited to participate in an ancillary qualitative study investigating the acceptability of the trial interventions. Willing participants will undergo a separate informed consent process for this study.

## Interventions

### Explanation for the choice of comparators {6b}

An inert placebo will be used as a comparator for memantine to separate the effect of this medicine from non-specific effects of being allocated and taking an oral medicine. Graded motor imagery will be evaluated against no graded motor imagery, as it was not considered possible to implement a sham that is both convincing and inert.

### Intervention description {11a}

#### Memantine

Oral memantine will be administered at 40 mg/day, or maximum tolerated dose, for 16 weeks, including titration and taper periods. The proposed dose is greater than that approved for moderate-to-severe Alzheimer’s disease (20 mg/day) and is informed by the protocol used by Gustin et al. [16]. By titrating to the highest tolerated dose up to 40 mg/day, the potential analgesic effects can be maximised while minimising the risk of adverse effects. The memantine dosing schedule comprises a 4-week titration period (5 mg/day for 4 days, 10 mg/day for 4 days, 15 mg/day for 4 days, 20 mg/day for 4 days, 25 mg/day for 4 days, 30 mg/day for 4 days, 35 mg/day for 4 days), an 8-week maintenance period (40 mg/day or maximum tolerated dose), and a 4-week taper period (5 mg reduction every 5th day). Memantine tablets are 10 mg, dosed morning and evening.

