#### Primary outcomes

The dual primary outcomes are pain intensity and pain interference. These outcomes were selected by the study consumer panel as they were determined to represent the most important aspects of improvement for CRPS. Pain intensity is the average pain intensity of the affected limb over the previous 7 days assessed using the 11-point numeric rating scale (NRS) [38], with scores of 0 indicating ‘no pain’ and scores of 10 indicating ‘worst imaginable pain’. This scale has demonstrated validity and reliability for use in chronic pain research [39]. Pain interference is assessed using the Patient-Reported Outcomes Measurement Information System (PROMIS) Pain Interference v1.1 [40], measured over the previous 7 days, with higher scores indicating greater pain interference. This measure has demonstrated reliability and validity across different pain populations [40, 41]. Both dual primary outcomes will be assessed as differences in mean final values at 16 weeks post-randomisation.

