
Continuous outcomes will be assessed as differences in mean final values at each timepoint; binary outcomes will be assessed as ratios of proportions.

PROMIS instruments use a *T*-score metric, in which 50 is the mean of the reference population and 10 is the standard deviation of that population [51]. All PROMIS scales, except for Global Health short form v1.1, will be measured using computer adaptive tests. Computer adaptive tests use item response theory to provide precise measurement using few items, and allow for scores that are directly comparable across different selections of items [52].

Pain intensity, pain interference, physical function, self-efficacy, and cognitive function will also be measured at 12 weeks to explore the mechanisms by which the graded motor imagery intervention exerts its effects. To evaluate the effect of adhering to the interventions, the following outcomes will also be measured: weekly measures of pain intensity, item 4 of the Credibility/Expectancy Questionnaire [53], Medical Form Confidence (weekly); International Physical Activity Questionnaire Short Form [54] (end of treatment only). See Methods for additional analyses (e.g. subgroup analyses) {20b} for further information.

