### Statistical methods for primary and secondary outcomes {20a}

#### Main analysis

All outcomes will be analysed according to the intention to treat principle. The analysis will involve estimation of the marginal mean effect of memantine compared to placebo and the marginal mean effect of graded motor imagery compared to no graded motor imagery on pain intensity and pain interference at 16 weeks. Additional information on the estimands of interest, including handling of intercurrent events, is provided in Table 2. As the trial has dual primary outcomes, interval estimates will be 97.5% confidence intervals. There will be no multiplicity adjustment for the two interventions as the factorial design answers two distinct questions.

**Table 2 Tab2:** Trial estimands

Estimand component	Definition
Interventions to be compared	To estimate the average causal effect of memantine, we will compare the mean outcome of trial participants allocated to receive memantine and graded motor imagery or memantine only with the mean outcome of trial participants allocated to receive placebo and graded motor imagery or placebo only To estimate the average causal effect of graded motor imagery, we will compare the mean outcome of trial participants allocated to receive memantine and graded motor imagery or placebo and graded motor imagery with the mean outcome of participants allocated to receive memantine only or placebo only
Population of interest	Adults with CRPS as defined by the trial eligibility criteria
Outcome of interest	Pain intensity, measured on a 11-point NRS; pain interference, measured with PROMIS pain interference v1.1
Summary measure (population-level)	Mean difference
Intercurrent events	All intercurrent events relating to memantine and graded motor imagery (e.g. intervention discontinuation, use of non-trial treatments) will be handled using a treatment policy strategy

For each of the dual primary outcomes, we will fit a longitudinal mixed-effects model that includes terms for the fixed effects of each intervention, the three follow-up timepoints, the intervention by time interactions, the two-way interaction between the interventions, and the baseline values of the outcome variables. In addition, the models will include terms for the fixed effects of the duration of CRPS (modelled as linear or linear with log transformation) and workplace compensation status, as well as random intercepts for trial participants.

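### The week-16 primary reads memantine in the last week of its taper, and no memantine-versus-placebo estimate is planned at the maintenance dose although week-12 data are collected

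*Protocol article*

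**What the plan says.** All places are in the protocol article, which states that it includes both the protocol and the statistical analysis plan.

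- **Course length (Intervention description, Memantine).** "Oral memantine will be administered at 40 mg/day, or maximum tolerated dose, for 16 weeks, including titration and taper periods".
- **Phases (same section).** "The memantine dosing schedule comprises a 4-week titration period", followed by "an 8-week maintenance period (40 mg/day or maximum tolerated dose), and a 4-week taper period (5 mg reduction every 5th day").
- **Primary endpoint (Outcomes, Primary outcomes).** "Both dual primary outcomes will be assessed as differences in mean final values at 16 weeks post-randomisation". The recall period is stated: "Pain intensity is the average pain intensity of the affected limb over the previous 7 days". Pain interference also uses the previous 7 days.
- **Week-12 data (Outcomes, after the list of secondary outcomes).** Pain intensity and pain interference, with three other scales, "will also be measured at 12 weeks to explore the mechanisms by which the graded motor imagery intervention exerts its effects".
- **Weekly data (same place).** "To evaluate the effect of adhering to the interventions, the following outcomes will also be measured: weekly measures of pain intensity".
- **Model (Statistical methods, Main analysis).** The fixed effects include each intervention, "the three follow-up timepoints" and the intervention-by-time interactions. The Objectives name weeks 16, 26 and 52.

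**The concern.** Week 16 is the end of the course for both factors, but it does not mean the same for each. The graded motor imagery sessions are spread over the 16 weeks. Memantine is at its highest dose up to week 12 and is then withdrawn in steps. The article justifies the target dose by the wish to maximise analgesia, yet it plans no comparison with placebo while participants are at that dose.

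What is at stake is the interpretation of a small or null memantine estimate. It could mean that the drug does not help, or that it helps at the maintenance dose and the benefit recedes as the dose falls. These lead to different conclusions about memantine in this condition, and the planned analyses would not tell them apart. A week-12 comparison added after unblinding would be post hoc and carry little weight.

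**Working it through.** **1. Timeline.** Inputs are from the Memantine section.
- Titration: 7 dose levels × 4 days = 28 days.
- Maintenance: 8 × 7 = 56 days.
- Taper: 4 × 7 = 28 days.
- Total: 28 + 56 + 28 = 112 days = 16 weeks, which reproduces the stated course length.

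Maintenance ends on day 28 + 56 = 84, the end of week 12. The taper ends on day 112, the end of week 16. If medication starts at randomisation, the 7-day recall at week 16 covers taper days 22 to 28 and the recall at week 12 lies wholly in maintenance.

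**2. Does the taper wording fit 28 days?** Stepping down from 40 mg by 5 mg gives seven levels above zero (35 to 5 mg).
- Levels lasting 4 days: 7 × 4 = 28 days, which fits.
- Levels lasting a full 5 days: 7 × 5 = 35 days, which does not.

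The interval can be counted either way, so the dose in the recall week is not fixed by the text.

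**3. Scheduled dose in the week-16 recall window**, for a participant who reached 40 mg/day:

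| Reading of the taper | Doses on taper days 22–28 (mg) | Mean (mg/day) | Share of 40 mg |
|---|---|---|---|
| 4-day steps, first cut on day 1 | 10,10,10,5,5,5,5 | 50/7 = 7.1 | 18% |
| 4-day steps, first cut on day 5 | 15,15,15,10,10,10,10 | 85/7 = 12.1 | 30% |
| 5-day steps, first cut on day 1 | 15,15,15,15,10,10,10 | 90/7 = 12.9 | 32% |
| 5-day steps, first cut on day 5 | 20,20,20,15,15,15,15 | 120/7 = 17.1 | 43% |

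The week-12 window is at 40 mg/day (100%) on every reading. The table describes the wording and recommends no schedule.

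**4. Is any planned analysis aimed at the maintenance dose?**
- Main model: three follow-up timepoints, which the Objectives name as weeks 16, 26 and 52. Week 12 is not among them.
- Week-12 scores: assigned to graded motor imagery mechanisms, and the Mediation analysis section covers graded motor imagery only.
- Weekly pain intensity: tied to adherence, does not include pain interference, and has no specified memantine contrast.
- Complier average causal effect: done only if non-adherence is significant, names no timepoint, and defines adherence against the prescribed dose, which includes the taper.

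None gives memantine versus placebo at the end of maintenance.

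**5. Illustration of what fading could cost.** The article gives no figure for how much benefit persists, so the retained share f is an assumption. Holding the design at its stated 90% power for 1 point (two-sided 2.5%), the effect is 2.241 + 1.282 = 3.523 standard errors, and power = Φ(3.523 f − 2.241).

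| f retained at week 16 | Power |
|---|---|
| 1.00 (full persistence) | 90% |
| 0.75 | 66% |
| 0.50 | 32% |
| 0.43 (proportional to dose, 17.1 mg) | 23% |
| 0.18 (proportional to dose, 7.1 mg) | 5% |

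The 90% is itself uncertain. With baseline adjustment at correlation 0.7, SD 2 and 182 participants, the standard error is 2 × 2 × √(1 − 0.49) / √182 = 0.212. Power for 1 point is then about 99%, and the last two rows become about 41% and 8%.

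**The case against.** The strongest reply is that week 16 is a coherent target. The intervention is defined as a 16-week course including its taper, Table 2 compares groups as allocated under a treatment-policy strategy, and week 16 is also the end of graded motor imagery. An effect that lasts to the end of the course is a legitimate thing to estimate. This stands, and it is why the primary need not move.

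A reader might infer that the trial has no on-drug estimate at all. The schedule does not support that: participants still have a reduced dose scheduled in the week-16 recall window. What is missing is an estimate at the maintenance dose.

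A reader might also take the 5% to 23% power range as a prediction. It is not. It assumes that benefit follows the dose taken in the last week, for which the article offers no evidence, and applies only to participants who reached 40 mg/day. The article also says that findings will be interpreted through estimates and intervals rather than claims of significance.

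Nor does the taper wording plainly contradict itself. Four-day levels fit 28 days, so the phrase is ambiguous.

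The weekly pain scores do span maintenance and could inform the question for pain intensity, but no memantine comparison on them is specified. Table 1, with the visit windows, is not shown, and medicine is sent to homes after randomisation, so the exact taper day at assessment may shift.

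**Conclusion.** The point holds as a gap in the planned analyses, and the primary endpoint is not in error. Maintenance ends at week 12, the week-16 recall falls in the last taper week at roughly 18% to 43% of the maintenance dose, and no memantine contrast at that dose is planned although the scores are collected. The timeline is exact on the article's figures. The dose range assumes a participant who reached 40 mg/day, started at randomisation and followed the schedule.

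The consequence is conditional. With full persistence of benefit nothing is lost. If benefit tracks dose the loss of power is severe, and week 16 could not separate an ineffective drug from one whose effect was lost on taper. The documents do not say where the truth lies. This is therefore an inexpensive improvement worth making, not a change on which the validity of the trial depends.

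**What to change.** - Keep week 16 as the primary timepoint, with its model and the sample size unchanged.
- Before unblinding, pre-specify the marginal effect of memantine versus placebo on pain intensity and pain interference at week 12 (end of maintenance) as a secondary estimate. Obtain it from the same form of mixed model with week 12 added as a follow-up level.
- In reports, describe the week-16 memantine estimate as an end-of-course, end-of-taper effect.
- Separately, reconcile the 4-week taper with the stated step interval in the Memantine section, because levels lasting a full 5 days do not fit 28 days. Which schedule applies is for the trial team to state.

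The cost is a wording change in the analysis plan, a registry update and one more secondary estimate per primary outcome. No new data are needed. Timing matters: recruitment is projected to finish in Q2 2026 and the final assessment is expected in Q2 2027, so the contrast can still be fixed while allocation to memantine is blinded.

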#### Placebo memantine

Placebo will be dosed according to the same schedule as memantine, including titration and taper periods, and dose individualisation. Placebo memantine tablets will differ from active memantine tablets only in the absence of the active ingredient and will be indistinguishable by sight, touch, or taste. The matched placebo is PROSOLV EASYtab SP (JRS Pharma, Weissenborn, Germany). It consists of 95–98% microcrystalline cellulose, 1.5–2.5% colloidal silicon dioxide, 0.5–2% sodium starch glycolate, and 0.3–1.0% sodium stearyl fumarate.

Trial medicines will be manufactured, packaged, and labelled to comply with Good Manufacturing Practice. The trial medicine will be dispensed by an independent trial pharmacist direct to participants’ homes. Each trial medicine kit will include a pill cutter to halve tablets during titration and taper periods, a medication schedule, and medication instructions.

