### Criteria for discontinuing or modifying allocated interventions {11b}

#### Memantine/placebo

The maximum tolerated dose (up to 40 mg/day) will be determined by the participant in consultation with the blinded trial physician and considers the participant’s willingness to continue the drug therapy despite adverse effects. Should participants need to temporarily suspend treatment due to intolerable adverse effects, they will be instructed to cease the medication for 48 h, at which point they will be reviewed by the trial physician. If the intolerable adverse effects have resolved, the participant will be instructed to resume the study medication at the highest tolerated dose before the onset of intolerable adverse effects. If the intolerable adverse effects have not resolved, the participant will be instructed to continue witholding the medication, with review by the trial physician every 48 h. The memantine/placebo therapy may be discontinued at the participant’s or physician’s discretion.

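### From 40 mg/day, the memantine taper's stated step (5 mg every fifth day) does not deliver its stated length (4 weeks) on the ordinary reading of the words

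*Protocol article*

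**What the plan says.** The Memantine section of Intervention description {11a} fixes the total course: "Oral memantine will be administered at 40 mg/day, or maximum tolerated dose, for 16 weeks, including titration and taper periods". It then divides the course into three parts.

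- Titration is listed level by level, beginning "a 4-week titration period (5 mg/day for 4 days, 10 mg/day for 4 days, 15 mg/day for 4 days" and continuing in the same way up to 35 mg/day.
- Maintenance is "an 8-week maintenance period (40 mg/day or maximum tolerated dose".
- The taper is "a 4-week taper period (5 mg reduction every 5th day". No dose levels are listed, and neither the day of the first cut nor the last dosing day is given.

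The section on placebo carries the schedule over: "Placebo will be dosed according to the same schedule as memantine, including titration and taper periods, and dose individualisation". It adds that each kit holds "a pill cutter to halve tablets during titration and taper periods, a medication schedule, and medication instructions". That schedule is not part of the article.

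The Primary outcomes section sets the reading time: "Both dual primary outcomes will be assessed as differences in mean final values at 16 weeks post-randomisation". Both measures look back over the previous seven days. The section on adverse event reporting {22} plans active weekly capture in weeks 1 to 16, then at weeks 26 and 52, with passive reporting alongside.

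**The concern.** Within one sentence the taper is defined twice, by its duration and by its rate. Given the starting dose, the rate determines the duration, so the two should match. On the usual meaning of the rate they do not.

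Three things depend on this. First, if the step governs, some days of active dosing fall after the 16-week treatment period and after weekly active capture of adverse events has ended. Second, if the length governs, dosing stops while 10 or 15 mg/day is still being taken, although the plan describes a stepwise taper. Third, the last week of the taper is the recall window of both primary outcomes, so the dose behind the primary reading differs with the interpretation.

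**Working it through.** **Inputs** (all from the Memantine section): starting dose 40 mg/day, cut size 5 mg, taper length 4 weeks = 28 days.

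**Checking the figures that do agree.** Titration: 7 levels × 4 days = 28 days = 4 weeks. Whole course: 4 + 8 + 4 = 16 weeks. Both reproduce.

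**The taper.** Number of cuts to zero: 40 / 5 = 8. Let *s* be the interval between cuts in days and *f* the taper day of the first cut. Then:

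- last dosed day = *f* + (8 − 1) × *s* − 1
- cuts made by day 28 = floor((28 − *f*) / *s*) + 1
- dose on day 28 = 40 − 5 × (cuts made by day 28)

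| Reading | Last dosed day | Cuts by day 28 | Dose on day 28 | Days beyond 28 |
|---|---|---|---|---|
| *s* = 5, *f* = 1 | 1 + 35 − 1 = 35 | 6 | 10 mg/day | 7 |
| *s* = 5, *f* = 5 | 5 + 35 − 1 = 39 | 5 | 15 mg/day | 11 |
| *s* = 5, *f* = 6 (after a full interval) | 6 + 35 − 1 = 40 | 5 | 15 mg/day | 12 |
| *s* = 4, *f* = 1 | 1 + 28 − 1 = 28 | 7 | 5 mg/day | 0 |
| *s* = 4, *f* = 5 | 5 + 28 − 1 = 32 | 6 | 10 mg/day | 4 |

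Only the fourth row reproduces the stated 28 days: seven levels from 35 down to 5 mg/day, each held for four days, with zero on day 29. It needs two choices that the text does not make. The fifth row shows that a four-day hold alone is not enough, because the first cut must also fall on taper day 1.

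**Mean dose on taper days 22 to 28, from 40 mg/day.** This is the recall window if dosing starts at randomisation and the assessment is at the end of week 16.

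- *s* = 4, *f* = 1: (3 × 10 + 4 × 5) / 7 = 50 / 7 = 7.1 mg/day
- *s* = 5, *f* = 1: (4 × 15 + 3 × 10) / 7 = 90 / 7 = 12.9 mg/day
- *s* = 5, *f* = 6: (4 × 20 + 3 × 15) / 7 = 125 / 7 = 17.9 mg/day

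The other two rows lie inside this range: 120 / 7 = 17.1 for *s* = 5, *f* = 5, and 85 / 7 = 12.1 for *s* = 4, *f* = 5.

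**The case against.** The best defence is that the phrase can be counted inclusively: hold each level for four days and cut on the fifth. With the first cut on taper day 1 this gives exactly 28 days and mirrors the seven four-day titration levels in the same sentence. That stands. A reader might infer that the rule cannot fit into four weeks at all, and the document does not support that. The defence is weakened by the sentence itself, which spells out every titration level as a four-day hold and then uses a different expression for the taper.

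The largest figures (day 40, 17.9 mg/day) need five more days at 40 mg/day after maintenance has ended, which stretches the stated eight weeks. This is fair. With the first cut on taper day 1 the overrun is 7 days, and 10 mg/day remains on day 28. The conflict is smaller but still there.

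The article also condenses a fuller protocol, and each kit contains a medication schedule that may settle the reading. This stands too, so a reader should not conclude that dosing at week 16 is undefined. Each reading gives a definite dose; the article does not say which reading applies. An unseen schedule does not remove the mismatch between two figures that the article does state.

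Finally, no bias is shown. Placebo follows the same schedule, and the estimand compares groups by allocation under a treatment policy strategy. That stands: the consequence shown is for the dose taken and for safety capture, not for the validity of the comparison.

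**Conclusion.** The point holds as a conflict between a stated length and a stated step. At five-day intervals from 40 mg/day, only 5 or 6 of the 8 cuts fall within 28 days, 10 or 15 mg/day remains on day 28, and dosing lasts 35 to 40 days, which is 7 to 12 days too long. One reading, four-day holds with the first cut on taper day 1, removes the conflict. The mean dose in the recall window is about 7, 13 or 18 mg/day according to the reading.

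This rests on two assumptions. The taper is meant to end at zero within the 16 weeks, which the article implies by including the taper in the course but does not say outright. Dosing is also taken to start at randomisation, so that the last taper week is the recall window.

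A reader might also infer a second contradiction from the individualised dose ("The maximum tolerated dose (up to 40 mg/day) will be determined by the participant in consultation with the blinded trial physician"), because the same steps from a lower dose reach zero sooner. The document does not support that. It does not say that every taper must fill 28 days, and it does not state that participants on lower doses begin the taper at week 12. Any dependence of exposure on tolerability comes from individualising the dose and would remain if the wording were clear. The sample size is unaffected.

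**What to change.** In the Memantine section, reconcile the taper length with the taper step so that one schedule follows from the text. State the day of the first reduction and the last dosing day. Check that the medication schedule and instructions in the kit, for active drug and placebo alike, say the same. Whether the length or the step is to change, and how, is for the sponsor's clinicians.

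The cost is a wording correction, plus a correction of the kit schedule if it differs. No participants, visits or data items are added. The daily medication diaries and pill counts already planned under {11c} need no change for this point.
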